**Fig. 1 Fig1:**
[figure not shown]
Flow diagram of trial design. MEP = a structured physiotherapy-led exercise programme; MEP-C – MEP together with an occupational therapist-led, person-centred cognitive intervention; TAU = treatment as usual

### Sample size estimation

The power calculation is based on the primary outcome, ADHD symptom reduction assessed using the World Health Organization (WHO) Adult ADHD Self-Report Scale (ASRS-v1.1) [32]. Postulating a mean difference in symptom reduction of 15% between the intervention and control groups, with 10.63% SD, 0.05 alpha, 0.8 power and expecting a 25% drop-out, gives a sample size of 120 participants. The actual sample size required for a power of 0.8 is 90 (= 120–120*25%). In case we have larger than 25% drop-out, we will recruit more participants to maintain the necessary power of 0.8.

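### The 90 completers (120 enrolled) said to be needed for 80% power do not follow from the stated 15% difference and 10.63% SD, which need about 9 per arm

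*Protocol article*

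**What the plan says.** The Sample size estimation section bases the calculation on symptom reduction measured with the ASRS-v1.1. The inputs are given in one sentence: "Postulating a mean difference in symptom reduction of 15% between the intervention and control groups, with 10.63% SD, 0.05 alpha, 0.8 power". With the drop-out allowance the text continues: "expecting a 25% drop-out, gives a sample size of 120 participants". It then states the requirement before drop-out: "The actual sample size required for a power of 0.8 is 90", obtained by taking 25% of 120 away from 120.

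The section also makes a recruitment commitment that rests on this number. If drop-out exceeds 25%, "we will recruit more participants to maintain the necessary power of 0.8".

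Elsewhere in the article, Design sets three arms of 40, Randomization and blinding sets a 1:1:1 ratio, and Analysis of quantitative data names ANOVA for comparing group means and t-test, Mann-Whitney U or Chi-squared tests for differences in change. The sample size section does not name the test, its sidedness, the pair of groups compared or any adjustment of alpha.

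**The concern.** The difference and the SD are both printed as percentages, so they can be divided directly. The result is a standardised difference of 1.41, which is very large. An effect of that size needs a small trial, yet the article reports that 90 completers are required to reach 80% power.

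This paragraph is the article's only justification of the sample size. A reader who trusts the inputs concludes that the trial has almost certain power for a 15% effect. A reader who trusts the 90 and the 80% concludes that the trial is just large enough. Both cannot be right, so nobody can tell which effect the trial was designed to detect. That matters most if the result is not significant, because the reader must then judge whether a worthwhile effect could have been missed. The top-up rule has the same weakness: it protects a count of 90 that the stated inputs do not require.

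**Working it through.** **Inputs, all from Sample size estimation unless noted**
- Difference in mean reduction: 15%
- SD: 10.63%, taken in the same unit because both are printed as percentages
- Alpha 0.05; two-sided is assumed because sidedness is not stated (one-sided is tried below)
- Power 0.80; drop-out 25%
- Three arms, 1:1:1 (Design; Randomization and blinding)

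**Step 1: the drop-out arithmetic.** 120 − 0.25 × 120 = 90, and 90 / (1 − 0.25) = 120. This reproduces. It corresponds to 40 enrolled and 30 completers per arm.

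**Step 2: the number needed from the stated inputs.**
- Standardised difference: d = 15 / 10.63 = 1.411
- Normal approximation: n per arm = 2 × (1.960 + 0.842)² / 1.411² = 7.88, so 8 per arm
- Exact power of the two-sample t-test (noncentral t): 8 per arm gives 0.747 and 9 per arm gives 0.802, so 9 per arm
- Three arms: 3 × 9 = 27 completers; 27 / 0.75 = 36 enrolled

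The stated 90 is 90 / 27 = 3.3 times this number.

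**Step 3: power at the stated size.** With d = 1.411, two-sided alpha 0.05:
- 30 v 30: 0.9997
- 60 v 30 (both exercise arms pooled v TAU): above 0.9999
- 45 v 45 (90 read as a two-group total): above 0.9999

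**Step 4: does any other reading give 90?** Exact t-test or ANOVA, 80% power unless noted:

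| Reading | Per arm | Three arms |
|---|---|---|
| One-sided, alpha 0.05 | 7 | 21 |
| Two-sided, alpha 0.05 | 9 | 27 |
| Two-sided, alpha 0.05/2 | 11 | 33 |
| Two-sided, alpha 0.05/3 | 13 | 39 |
| Two-sided, alpha 0.05/9 | 16 | 48 |
| SD multiplied by √2 | 17 | 51 |
| ANOVA, means 0/15/15 | 9 | 27 |
| ANOVA, means 0/7.5/15 | 11 | 33 |
| Power raised to 0.999 | 27 | 81 |

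None reaches 90 at 80% power. Even 99.9% power needs only 81.

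**Step 5: what 90 completers would be consistent with.** Solving the t-test for d at 80% power and two-sided alpha 0.05:

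| Comparison | Detectable d | In points if SD is 10.63% (d × 10.63) | SD that makes 15% detectable (15 / d) |
|---|---|---|---|
| 30 v 30 | 0.736 | 7.8 | 20.4% |
| 60 v 30 | 0.633 | 6.7 | 23.7% |
| 45 v 45 | 0.597 | 6.3 | 25.1% |

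If alpha were shared over two comparisons with TAU (0.025 each), 30 v 30 would detect 0.814 SD, or 8.7 points at an SD of 10.63%.

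**The case against.** The best defence is that the fault may be a single misprinted unit and the 90 may be right. Suppose 10.63 is an SD in ASRS points and 15% is a reduction relative to the baseline mean. With an assumed baseline mean of 52 points, the difference is 0.15 × 52 = 7.8 points, d = 7.8 / 10.63 = 0.734, and 30 per arm gives power 0.798, which matches the printed figures. For assumed baselines of 48 and 55 points, the exact t-test needs 36 and 28 per arm. This is plausible, but the article gives no baseline mean and prints the SD as a percentage. It is a guess at how the error arose, and the text would still need correcting.

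A second point is that, on the literal inputs, the error is conservative: 30 completers per arm exceed what 80% power needs, and the top-up rule could not leave the trial underpowered. That stands. The check does not show that the trial is too small. It shows that the text gives no reliable basis for judging.

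A third point is that the source of the SD and any sharing of alpha may sit in a full protocol or analysis plan that is not shown. That also stands, so the 0.81 SD figure applies only if alpha is shared. But the article states the inputs, the result and that one gives the other. That is a wrong statement, which another document cannot repair.

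**Conclusion.** The concern holds. The stated inputs require 27 completers (36 enrolled), not 90 (120), and the stated size would give 99.97% power for a pairwise comparison, not 80%. Two-sided testing is an assumption, but it does not matter: every variant tried falls well short of 90.

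The inputs and the sample size are therefore incompatible. The document does not show whether the difference, the SD, its unit or the 90 is in error. If 30 completers per arm is taken as fixed, what the trial can claim at 80% power and two-sided 5% is a difference of 0.74 SD between one exercise arm and TAU. That equals 15% only if the SD is about 20.4%, nearly twice the printed value.

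**What to change.** Keep enrolment at 120 and rewrite the Sample size estimation paragraph from the original calculation:

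- State the difference and the SD on the same scale as the analysed ASRS score (points or percentage change), with the source of the SD.
- Name the test, its sidedness and the comparison powered, for example each exercise arm v TAU with 30 v 30 completers.
- Report the detectable difference: 0.74 SD at two-sided 5%, or 0.81 SD if alpha is to be shared over two comparisons with TAU.
- If the original inputs cannot be recovered, say so, and label the detectable difference as worked out from the fixed sample size. Data collection began in March 2021 (Discussion in the abstract), so it would not be the original rationale.
- Tie the top-up rule to the corrected number of completers.

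The cost is one reworded paragraph and a short amendment, with no extra participants. The restated effect may look less favourable than the present text suggests.

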### Participants

Recruitment will primarily be conducted by the General Psychiatry outpatient clinic and the clinic for young adults at Örebro University Hospital, Örebro, Sweden. Eligible persons will receive written and oral information about the study and a consent form when visiting the clinic. Participants will also be recruited via the following channels: the 1177 website (the official website for all county-based health care in Sweden); the Örebro County Facebook account; and the National Association of Neurodevelopmental Disorders, Riksförbundet Attention. Interested persons will be invited to contact the research team to receive written and oral information about the study and a consent form. Individuals who agree to participate in the study and are eligible according to the inclusion and exclusion criteria will be included. To assess eligibility for inclusion, their medical history will be retrieved from the medical records.

Inclusion criteria: Diagnosed with ADHD; age 18–65 years; stable medication or no medication.

Exclusion criteria: Ongoing depression (Montgomery-Asberg Depression Rating Scale, Self-Assessment (MADRS-S) score > 21), suicidality, bipolar disorder, psychosis, substance abuse, severe autism, reported threatening behaviour, and severe physical illness, as well as inability to read/understand Swedish.

### Randomization and blinding

Individuals meeting the inclusion criteria will be randomized into three groups (two intervention groups and one control group) using the Smart-Trial (S-T) electronic data capture platform hosted by Region Örebro County. Randomization will be performed in a 1:1:1 ratio using a block of 6 (9 or 12 to be determined). Stratification will not be applied. During the clinician-rated assessment interview, participants will be instructed not to disclose their group assignment. Due to the nature of the intervention involving structured physical exercise with or without additional person-centred cognitive skills training, blinding of participants to the interventionists in the planned RCT will not be feasible. The individuals collecting the physical tests will also not be blinded to group allocation. However, the data analysts will be blinded to group allocation during the analysis process.

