**Discussion:**

Data collection began in March 2021. The final 12-month follow-up is anticipated to be completed by autumn 2024.

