### Outcome measures

See Table 3 for a summary of measures given by time point.

**Table 3 Tab3:** Measures by time point

	Completed by:	Visit 1	3 weeks	6 weeks	9 weeks	12 weeks (end of the intervention)	6- month follow- up	12- month follow- up
Informed consent to trial participation	PT							

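### The block size is left open between 6, 9 and 12 after enrolment began; if one size was fixed and known to open-label staff, 11% to 20% of allocations were certain in advance, against about 2.5% with concealed mixed sizes

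*Protocol article*

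**What the plan says.** The section Randomization and blinding says that participants will be "randomized into three groups (two intervention groups and one control group) using the Smart-Trial (S-T) electronic data capture platform". The scheme is then given as "Randomization will be performed in a 1:1:1 ratio using a block of 6 (9 or 12 to be determined", followed by "Stratification will not be applied". So there is one sequence for the whole trial, planned for 120 participants (Sample size estimation: "gives a sample size of 120 participants").

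The same section says that "blinding of participants to the interventionists in the planned RCT will not be feasible" and that "The individuals collecting the physical tests will also not be blinded to group allocation". The data analysts are to be blinded. Nothing is said about random variation of the block size, or about who is told it.

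In Table 3 the row "Informed consent to trial participation" carries the code for the physiotherapist. The section on the START intervention has physiotherapists leading the exercise in both active arms. Under Participants, recruitment runs mainly through two clinics of one hospital, and people who refer themselves contact the research team. Under Data storage, randomization takes place in the electronic platform directly after inclusion.

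On timing, the abstract says "Data collection began in March 2021". The article appeared on 25 September 2023.

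**The concern.** Two things look wrong.

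First, participants are randomized directly after inclusion, so some block rule must have been running since early in the trial. An article published two and a half years after data collection began should not still call that rule undecided.

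Second, electronic allocation hides the next assignment but not a regular pattern. With equal blocks of one known size, anyone who has counted the allocations so far knows the last place in every block, and sometimes more. The arms here are visible once assigned, and there is a single sequence to follow. The profession listed for consent also delivers the exercise. Eligibility terms such as severe autism and severe physical illness leave room for judgement before randomization. Someone who knows the next arm could time or steer an enrolment, even without meaning to.

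At stake is the comparability of the arms. The outcome used for the power calculation, ASRS-v1.1, is self-reported in an open trial, and the article's own Discussion already concedes expectation bias. Selection at entry would be a separate bias, and blinding the analysts does not remove it.

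**Working it through.** The article states no predictability figure, so there is none to reproduce. The check asks what each reading of the block sentence would imply.

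**Inputs from the article.** Three arms at 1:1:1; block size 6, 9 or 12; no strata; 120 participants planned.

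**Assumptions not in the article.** The guesser knows the block size and every earlier allocation in order. This is the worst case.

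**Formula.** Let b be the block size and m = b/3 the places per arm. An allocation is certain when only one arm is left in the block. The expected number of certain allocations per block is therefore the expected length of the run of identical arms that ends the block:

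1 + (m−1)/(b−1) + (m−1)(m−2)/[(b−1)(b−2)] + …

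**One fixed size.**

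- b = 6, m = 2: 1 + 1/5 = 1.200; 1.200/6 = 20.0%; 0.200 × 120 = 24 participants.
- b = 9, m = 3: 1 + 2/8 + 2/56 = 1.286; 1.286/9 = 14.3%; about 17 of 120.
- b = 12, m = 4: 1 + 3/11 + 6/110 + 6/990 = 1.333; 1.333/12 = 11.1%; about 13 of 120.

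**Weaker forms of prediction**, by exact enumeration under the same assumptions:

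| Fixed block size | Arm certain | At least one arm ruled out | Exercise versus usual treatment certain | Best guess correct (33.3% by chance) |
|---|---|---|---|---|
| 6 | 20.0% | 46.7% | 28.9% | 56.1% |
| 9 | 14.3% | 35.7% | 21.4% | 53.2% |
| 12 | 11.1% | 28.9% | 17.0% | 51.2% |

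**Sizes 6, 9 and 12 mixed at random with equal probability.** This was simulated with 300 trials of 120 participants. The guesser knows which three sizes are in use and the full history, but not the order of the sizes. The arm was certain for 2.5% of allocations, or 0.025 × 120 = 3 participants. This counts only certain allocations; an attentive guesser would still be right more often than one time in three.

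**Comparison.** 20.0/2.5 = 8, so concealed mixing reduces certain allocations about eightfold against a fixed block of 6, and about fourfold (11.1/2.5 = 4.4) against a fixed block of 12.

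**Price of mixing.** An unfinished block of 12 can leave two arms at most 12/3 = 4 participants apart.

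**The case against.** The case against has several parts.

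- **The text does not say that one size is fixed.** The sentence can mean one size not yet chosen, or 6 used together with other sizes. A reader might infer that staff can predict one allocation in five. That is the top of the range, reached only if the size is 6 throughout. This objection stands.
- **Prediction needs knowledge that the article does not give to recruiters.** Only part of the research group has access to the platform, the principal investigator approves each role, and participants enter through two clinics and several self-referral routes. One person may never see the whole sequence. This stands as a reason to treat the percentages as upper limits. It does not remove the risk, because the same section says the system shows each participant's status clearly to those who do have access.
- **The consent entry is thin evidence.** The column that says who completes each measure is irregular in the text at hand; it also shows the physiotherapist against a depression self-rating. Taking consent does not prove discretion over who enters. This stands in part: the entry shows that recruiting and treating roles may overlap, not that anyone steered enrolment.
- **A reader might infer that publishing the block size lets staff predict.** The dates do not support that. Follow-up at 12 months ending in autumn 2024 puts the last enrolment at about summer or autumn 2023, near the date of publication. What matters is what staff knew during recruitment.
- **A reader might infer that selection bias could never be detected, or that every primary outcome is self-reported.** Neither holds. The planned baseline comparisons could show imbalance in measured variables, though not in motivation or other unmeasured traits. The two clinician-rated global scales are also listed as primary.
- **An article may leave block details to a fuller document.** That would excuse silence. Here the article does state a block scheme, and states it as unsettled while it was in use.

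**Conclusion.** The point holds in a conditional form. The article describes a single unstratified sequence in an open trial, names a block size, leaves that size unsettled after the trial had started, and mentions neither variation nor concealment of sizes. If one size was fixed and known to someone following past allocations, the certain share is 20% at size 6, 14% at size 9 and 11% at size 12. Randomly mixed and concealed sizes would bring it to about 2.5%.

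The fixed-size figures rest on full knowledge of size and history, which the article neither states nor excludes. They measure what could be predicted, not bias that has occurred. The point is still worth acting on: the better method is simple and cheap, and readers need the actual scheme to judge allocation concealment.

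**What to change.** 1. For any allocations still to be made, including the extra recruitment that Sample size estimation foresees if drop-out exceeds 25%, set the platform to draw block sizes 6, 9 and 12 at random.
2. Withhold the sizes from everyone who recruits, takes consent or treats.
3. Replace the open wording on block size with the scheme actually used since the first participant, including any change of size and who knew it.
4. If a fixed size was used and known to those staff, report this as a limitation on allocation concealment.

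The cost is a setting in the randomization module and one or two sentences of text. The downside is that arm sizes may differ by a few participants at the end. If recruitment has already finished, the first step has nothing to act on and the reporting steps remain.

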### Intervention: the START intervention programme

The intervention consists of a MEP with and without cognitive skills training, which includes strength, cardio and flexibility training. One arm of the study will receive physical exercise together with cognitive skills training to address impaired executive function in everyday life, which is common among people with ADHD. This training is an occupational therapist-led, person-centred cognitive intervention aiming to improve time management skills, planning and organization. The physical exercise will consist of interval training, following a structured programme including both aerobic/endurance exercises and resistance exercises/strength training (see Table 1). The occupational therapy intervention will depend on the participant’s personal goals (Table 2).

**Table 1 Tab1:** Structure of the interval training of the START intervention

START intervention exercise (total 45 min)		
Type/purpose	Duration (% of total)	Content
**Warm-up**	6 min (13.5%)	Light exercise, cycling, cross-training, walking or full body movements. “Focus on how you are today.”
**Cardio**	6 min (13.5%) (3 × 1-min exercise intervals, 1 min active rest between each interval)	Cycling, running/fast walking or jumping
**Resistance training**	23 min (51%) (1 min exercise + 20 s rest x 5 exercises in 3 rounds. 1 min rest between each round.)	Exercises for different muscle groups: lower body, upper body, core and balance. All groups are represented in each round, but exercises may vary. Number of repetitions are controlled by time limits and can vary with weight.
**Cool-down and flexibility**	10 min (22%)	Cool-down with light exercise, cycling, cross- training, walking or full body movements. Stretching exercises for larger muscle groups used in the resistance training. “Focus on how the body feels.”

**Table 2 Tab2:** Occupational therapy intervention

Session	Contents
1	Assessment of occupational performance using the Canadian Occupational Performance Measure (COPM): includes ranking and prioritization of a maximum of five activity-based intervention goals. The goals are based on the participant’s estimation of level of satisfaction with the performance, and value in daily life. Assessment of Satisfaction with Daily Occupations-Occupational Balance (SDO-OB). The participant and the occupational therapist agree on the goal(s) that should be focused in the intervention.
2 to approx. 5	Intervention period. The number of sessions is based on the occupational therapist’s judgement of need depending on the goals set. Normally one session is held every second week. The intervention is focused on cognitive skills training using strategies targeting the activity limitations of the participant. This may include, but is not limited to: use of compensatory aids for planning and organization such as calendar, alarms and time visualization aids. The aim is for the participant to learn how to prioritize and estimate time, and build strategies to reach occupational balance in daily life (meaning balance between activity, recovery and sleep). For each session, the participant has home assignments, such as to try a new strategy or to keep a time diary to gain awareness of occupational patterns and occupational balance.
6	Evaluation of goal attainment using the COPM. Assessment using the SDO-OB.

**Type of intervention: MEP** – a structured physiotherapy-led exercise programme; or **MEP-C** – MEP together with an occupational therapist-led, person-centered cognitive intervention.**Dose, MEP**: Physical exercise for 45 min, three times a week for 12 weeks. **Dose, MEP-C:** Occupational therapy for 60 min approximately six times (every second week) during the 12-week period depending on participant’s goals related to the intervention; and physical exercise for 45 min, three times a week for 12 weeks.**Dose, MEP**: Physical exercise for 45 min, three times a week for 12 weeks. **Components of physical exercises, MEP and MEP-C**: All exercise sessions will have the same structure and consist of endurance, strength and flexibility training. Desired heart rate (HR) range will be 60–90% of maximum HR. In order to track HR during all sessions, both in the clinic and at home, the participants will have a Polar Heart Rate Monitor, model H10 (Polar Electro Oy, Kempele, Finland), connected to their mobile phone. Each exercise session will start with 5–10 minutes’ **warm-up** on an ergometer or using body movements. Next will be **endurance exercises** in three to five intervals of 1 min work and 1 min active rest between each interval. The **strength training exercises** will consist of five different exercises with 1-minute intervals between exercises, in three rounds. These strength exercises may vary depending on the location, indoors or outdoors. However, they will always include one exercise mainly for leg strength, for example squats or lunges; one exercise for arms and shoulders, for example shoulder press with barbell or bench press; one core exercise, for example crunches or the plank; and one balance challenge, for example standing on one leg. The participants will be encouraged to do as many repetitions as possible in 1 min and therefore the load of the exercise can be altered depending on the number of repetitions the participant can manage. In the cool-down, in the warm-up and during stretching the participant will be encouraged to sense the feeling of the body and their overall feeling.**Components of the cognitive intervention of the MEP-C**: As previously mentioned, the cognitive intervention will be conducted by an occupational therapist on approximately six occasions during the 12-week period. Based on self-prioritized goals concerning structure, planning and organization in everyday life, a treatment plan for cognitive skills training will be drawn up. This will form the basis of the treatment. (Examples of such goals are: to arrive on time for training, or to create the space for physical activity in one’s everyday life through improved time management.)**Sequences**: The training sessions will take place either in the training facilities at the outpatient clinic or outdoors in a nearby park. Each session will follow a specific structure.**Modifications**: Alternative exercises will be suggested by the instructors when needed. Participants will be allowed to perform to the best of their ability, with encouragement from the physiotherapists to use maximum effort.**Selection of instructors**: The instructors for the physical exercise sessions will be licensed physiotherapists at the Unit for Psychiatric Physiotherapy, Region Örebro County, who are experienced in working with persons with ADHD. The instructors for the cognitive intervention will be occupational therapists with experience of both working with persons with ADHD and using the Canadian Occupational Performance Measure (COPM) as person-centred tool [33, 34].**Home practice**: In addition to the physiotherapist-led group, the participants will be expected to exercise individually once a week, to the extent needed to reach 150 minutes’ exercise per week. Participants receiving cognitive skills training will be given home assignments, primarily to implement compensatory cognitive strategies in daily life.**Fidelity**: Training adherence will be noted by the treating physiotherapist and occupational therapist. Group adherence to physical activity will be calculated as the number of patients attending 50% of the sessions. To maintain physical exercise for at least 150 min per week, the HR monitor connected to the participants’ mobile phone will gather the time in an HR zone of > 60%. Attendance rate over the intervention period will be calculated as a mean of the individual percentage.**Control group**: Participants randomized to the control group will continue with their TAU. This will include any ongoing pharmacological and/or non-pharmacological treatment that does not include physical exercise or cognitive skills training during the 12-week period. After the 12-week data collection, the participants will be offered physiotherapy-supported training outside the framework of the study.
